## Abstract

**Introduction:**

The transition from low to high altitude environments is associated with a multifaceted series of physiological and psychological alterations that manifest over time. These changes are intricately intertwined, with physiological acclimatization primarily mediated through the regulation of hypoxia-inducible factor (HIF), which orchestrates the expression of critical molecules and hormones. This process extends to encompass the epigenome, metabolism, and other regulatory mechanisms. In the realm of psychological acclimatization, chronic hypoxia and changes in atmospheric pressure at high altitudes may contribute to decreased levels of neurotransmitters, with potential implications for mental health, particularly in relation to sleep quality. Despite significant advancements in our understanding of plateau acclimatization mechanisms in recent years, there remain many uncertain factors that necessitate further research.

**Methods:**

This study is a single-center prospective observational study. It aims to utilize a series of physiological and medical instruments in conjunction with internationally recognized physiological and psychological questionnaires to monitor the dynamic shifts in the acclimatization ability of doctors from Peking Union Medical College Hospital. The monitoring will occur at seven distinct time points: pre-departure from Beijing, 1–7 days post-arrival at the Tibetan plateau during the acute phase of plateau hypoxic stress, and during the chronic phase of plateau hypoxic stress at 2 weeks, 3 months, 6 months, 12 months of residency in Tibet, and post-return to Beijing. Concurrently, a spectrum of omics analyses will be conducted, including comprehensive genomic, proteomic, and metabolomic assessments of blood leukocytes, fecal, and oral samples.

## Introduction

1

More than 140 million people live at high altitude (above 2,500 m) (1). Among them, the major indigenous high-altitude populations live on the Andean, Tibetan, and east African plateau, where they experience the unique stress of hypobaric hypoxia (2).

Nowadays, more and more people are traveling to high altitude areas. The transition from low to high altitudes precipitates a multitude of physiological and psychological alterations in the human body, which may cause acute mountain sickness, high-altitude cerebral edema, and high-altitude pulmonary edema and so on (3). However, it has been established that mammals have evolved pivotal adaptive mechanisms to mitigate hypoxia, including enhanced ventilation, cardiac output, vascular proliferation, and the augmentation of circulating red blood cells. At the cellular level, ATP depletion responses are inhibited, and metabolic pathways are modulated to reestablish oxygen homeostasis (4). Furthermore, human responses to acute hypoxia include the activation of the adrenergic system and tachycardia, while hypoxic pulmonary vasoconstriction elevates pulmonary artery pressures. Over time, autonomic nervous system adaptations lead to a reduction in tachycardia, safeguarding the myocardium from excessive energy expenditure. Long-term exposure to high altitude results in cardiac adaptations with no obvious dysfunction (5).

The molecular underpinnings of altitude acclimatization have garnered considerable attention, with current research indicating that hypoxia-inducible factors (HIFs) play a pivotal role in orchestrating the expression of messengers and hormones, such as erythropoietin, vascular endothelial growth factor, and glucose transporters, in response to hypoxia (6). Moreover, the response to hypoxia encompasses a plethora of molecular and cellular alterations, including epigenetic modifications, non-coding RNA expression, metabolic shifts, signaling pathways, and various homeostatic mechanisms to ensure cellular survival under hypoxic stress (7).

Psychological alterations also accompany the physiological responses to hypobaric hypoxia and atmospheric pressure changes at high altitudes. Studies have indicated a correlation between increasing altitude and the prevalence of depression, attributing this to the challenging environmental and living conditions prevalent in high-altitude regions (8). Hypoxia and atmospheric pressure fluctuations may diminish serotonin levels in the brain (9), thereby compromising emotional regulation, potentially elevating the risk of depression (10). Additionally, sleep quality degradation is a common physiological effect at high altitudes, posing a significant threat to the physical and mental well-being of individuals residing or traversing these regions (11).

Despite the significant strides made in unraveling the molecular mechanisms of altitude acclimatization, the determinants of successful hypoxic acclimatization and the etiology and risk factors of altitude-related diseases remain elusive (12). Furthermore, research on psychological acclimatization to high-altitude environments is limited, warranting further exploration. Therefore, this study endeavors to elucidate the regulatory pathways that underpin the physio-psychological acclimatization of human beings in the Tibetan plateau hypoxic environment, with the aim of informing the development of optimized or novel preventive strategies for individuals ascending to high altitudes. The findings are anticipated to enhance the understanding of altitude sickness and potentially refine its treatment strategies.

## Method

2

### Design

2.1

This study is a single-center prospective observational study. It is intended to employ a suite of physiological and medical instruments in conjunction with internationally recognized standardized physiological and psychological questionnaires to dynamically monitor the physiological and psychological acclimatization of medical professionals from Peking Union Medical College Hospital. The monitoring will be conducted at seven key time points: prior to departure from Beijing, within 1–7 days post-arrival in Tibet during the acute phase of plateau hypoxia stress, during 2-week, 3-month, 6-month, and 12-month stays in Tibet during the chronic phase of plateau hypoxia stress, and upon return to Beijing.

The physiological parameters to be assessed include blood pressure, heart rate, fingertip venous oxygen saturation, hemoglobin concentration, hematocrit, physical phenotype, electrocardiogram conduction, cardiovascular function, and pulmonary function. Concurrently, questionnaires will be administered to assess acute mountain sickness, sleep quality, and emotional state. Blood, fecal, oral, and urine samples will be collected for further analysis, encompassing blood biochemical measurements, blood leukocyte whole gene expression profiling, blood proteomics, blood metabolomics, fecal metagenomics, fecal metabolomics, oral microbiota metagenomics high-throughput sequencing, and urine microprotein detection. Additionally, fundus examination and a six-minute walk test will be conducted.

In the present study, we aim to integrate the multi-omics sequencing outcomes obtained at seven distinct temporal intervals with the fluctuations observed in a array of biomarkers at corresponding time points. The objective is to delineate small molecules that are intrinsically linked to high-altitude acclimatization and to investigate the underlying molecular pathways. Concurrently, we propose to conduct a comparative analysis of omics sequencing data from groups stratified based on varying detection indicators across different time points. This approach is intended to elucidate the molecular mechanisms that may underpin the disparities in detection indicators. It is anticipated that these analytical endeavors will contribute to a more nuanced comprehension of altitude-induced illness and the physiological processes associated with altitude acclimatization. The trial design is presented in Figure 1, while the subsequent sections provide a comprehensive and detailed description of our trial.

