### Study population

2.2

The study will recruit 17 eligible medical professionals from Peking Union Medical College Hospital who are qualified to support Tibet and meet the basic requirements for physical examination, with a gender distribution of 10 males and 7 females. Participants must be between the ages of 20 and 65 years, able to provide written informed consent, and willing to cooperate. The inclusion and exclusion criteria will be strictly adhered to, ensuring the integrity and relevance of the sample.

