### Statistical analysis of detection indicators

2.5

SPSS V.26.0 will be used as the statistical software. Quantitative data with a normal distribution will be presented as means with standard deviations and will be compared between groups with the use of Student’s t-test or the rank-sum test. Quantitative data that do not follow a normal distribution or homogeneity of variance will be presented as median and IQR, and comparisons between groups will be performed by the Mann–Whitney U test. Enumeration data will be presented as ratios and percentages, and χ^2^ tests will be used for comparison. Two-tailed *p* < 0.05 is considered statistically significant.

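### Comparing omics data between groups split on continuous or scored indicators wastes power at n = 17; the measured value should carry that analysis

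*Protocol article*

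**What the plan says.** The Design section (2.1) sets out two omics-indicator analyses. The first integrates the omics results "with the fluctuations observed in a array of biomarkers at corresponding time points" and aims to find molecules and pathways linked to acclimatization. The second, run in parallel, is a "comparative analysis of omics sequencing data from groups stratified based on varying detection indicators across different time points". Its stated purpose is to "elucidate the molecular mechanisms that may underpin the disparities in detection indicators".

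Section 2.2 fixes the size: "The study will recruit 17 eligible medical professionals". Section 2.1 sets seven visits.

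Most indicators in sections 2.1 and 2.3 are continuous or scored: blood pressure, oxygen saturation, hemoglobin, hematocrit, FEV1, walk distance, sleep and mood scales, and biochemistry. A few are categorical by nature, such as fundus hemorrhage or edema, and acute mountain sickness when reported as an incidence.

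The article does not say how the groups are formed. Its only significance level, two-tailed 0.05, is in section 2.5, which covers the indicators themselves. The omics sections (2.4.1 to 2.4.6) name no threshold. Section 2.4.1 names DESeq2 or EdgeR for expression data, and section 2.4.6 mentions correlations across the omics layers.

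**The concern.** Once a continuous indicator has been turned into a group label, everyone within a group counts as the same and two people on either side of the line count as different. With a large cohort the price may be tolerable. With 17 people a median split gives 8 against 9, and outer tertiles give 6 against 6 with the middle five dropped.

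The article ties its explanation of differences in the indicators to this comparison, so the lost power falls on a central aim. Sections 3 and 5 already concede that 17 people strain the statistics. That is a reason not to give up more information in the analysis.

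A second, conditional risk concerns false positives. If the grouping were chosen after the data had been seen, one indicator would offer more than one test of the same question. False discovery rate control across genes or metabolites within one grouping would not cover that choice.

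**Working it through.** The article states no power, effect size or sample-size calculation, so there is no figure to reproduce.

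**Inputs.** n = 17 (section 2.2). Two-sided 0.05 (section 2.5, borrowed for illustration because the omics sections give no level). Assumed: one indicator x and one omics feature y, bivariate normal with correlation r, at one visit.

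**Tests compared**, by simulation with 40,000 replicates per setting:
- Measured value: t = r̂·√((n − 2)/(1 − r̂²)) on n − 2 = 15 degrees of freedom, where r̂ is the sample correlation.
- Median split: order people by x, then a two-sample t-test of y, lowest 8 v highest 9.
- Outer tertiles: the same test, lowest 6 v highest 6.

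**Power with the cut fixed in advance:**

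| True r | Measured value | Median split | Outer tertiles |
|---|---|---|---|
| 0.4 | 37% | 23–24% | 27% |
| 0.5 | 56% | 36% | 41% |
| 0.6 | 76% | 51% | 58% |
| 0.7 | 92% | 69–70% | 76–77% |

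At r = 0.5 the median split costs 56 − 36 = 20 points and outer tertiles 56 − 41 = 15. At r = 0.6 the costs are 76 − 51 = 25 and 76 − 58 = 18.

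**Rough cross-check.** The large-sample efficiency of a median split is 2/π = 0.64. Since 17 × 0.64 ≈ 10.9, the split uses the data about as well as 11 people analysed on the measured value.

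**Stricter threshold.** At alpha 0.001, closer to what omics screening demands, power at r = 0.7 is about 45% on the measured value and 12% for the median split.

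**Less favourable settings for the proposed analysis.** A rank correlation at r = 0.5 keeps about 49%, still above either split. If the truth is a step at the median rather than a line (y = 1.2 × [x above the median] + standard normal error), the continuous test has about 39% power and the median split about 43%. The continuous test then loses about 4 points.

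**False positives at r = 0.** Each fixed split, and the continuous test, rejects about 5%. Taking whichever of the median split or outer tertiles is significant rejects about 7.5–8%, roughly 1.5 times nominal.

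**The case against.** The strongest reply is that the grouped comparison is an addition and not the only analysis. Section 2.1 also links omics to indicator fluctuations, and section 2.4.6 plans correlations. This stands: a reader might infer that measured values are discarded throughout, and the article does not support that. But section 2.1 gives the task of explaining differences in the indicators to the grouped comparison, so the loss still matters there.

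Three further inferences are tempting and should not be drawn:
- That every indicator is split at every visit. The wording allows this, but it also fits selected indicators or trajectories.
- That each contrast is tested at an unadjusted 0.05. That level is given for the indicators, where values "will be compared between groups with the use of Student’s t-test or the rank-sum test"; no level is given for omics.
- That false positives are several times nominal. Searching every cut that leaves at least 4 per side would reject about 22% under no association, but the article neither states nor implies such a search. A cut rule may properly sit in a fuller document that is not shown, so its absence here is not a fault.

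Grouping is also natural for categorical indicators. Comparing people with and without acute mountain sickness is an ordinary reading of the sentence, and the point does not touch it.

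Finally, the linear normal model favours correlation. That is fair, but in the rank and step checks above the disadvantage is absent or small.

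**Conclusion.** The point holds for continuous and scored indicators, as an inexpensive improvement to a stated method. It is neither an error of fact nor a contradiction. With 17 people, a pre-fixed median or outer-tertile split costs roughly 15 to 25 points of power at correlations of 0.5 to 0.6. No choice between these cuts in an unseen analysis plan would recover it.

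The size rests on assumed correlations, a linear bivariate-normal relation, one feature at one visit, and two-sided 0.05. The direction is the same at every non-zero correlation tried. It reverses slightly under a pure step near the median.

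The false-positive risk is secondary and conditional. It arises only if the cut is chosen after seeing the data, and is about 7.5–8% for a choice between two common splits.

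**What to change.** In section 2.1, for continuous or scored indicators, make the primary omics-indicator analysis an association with the measured value, or with its change from the pre-departure visit, entered as a continuous covariate. Use ranks or logs where the indicator is skewed. DESeq2 and edgeR accept such a covariate for the expression data. The proteomic, metabolomic and metagenomic layers need an equivalent linear or rank model. State how repeated visits from the same person are handled, for example by a participant term or by analysing change at a named visit.

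Keep group comparisons for naturally categorical indicators (acute mountain sickness, fundus hemorrhage or edema) and for cut-offs fixed before the omics data are opened. Label any other split descriptive.

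The cost is a rewording of section 2.1 and a different model specification, with some extra work to specify the model outside the expression data. No new participants, visits or assays are needed. The downside is that a linear or monotone trend is assumed, so a pure threshold effect is detected slightly less well. Descriptive plots by group can still show one.

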**Figure 1 fig1:**
[figure not shown]
Flowchart of the study process.

### Study population

2.2

The study will recruit 17 eligible medical professionals from Peking Union Medical College Hospital who are qualified to support Tibet and meet the basic requirements for physical examination, with a gender distribution of 10 males and 7 females. Participants must be between the ages of 20 and 65 years, able to provide written informed consent, and willing to cooperate. The inclusion and exclusion criteria will be strictly adhered to, ensuring the integrity and relevance of the sample.

#### Inclusion criteria

2.2.1

(1) Healthy individuals aged 20–65 years.(2) They can sign a written informed consent and is willing to cooperate.(3) They have the qualification to aid Tibet and meet the basic requirements of physical examination for aid to Tibet.(4) There are no acute or chronic illnesses, such as asthma or pulmonary edema.

#### Exclusion criteria

2.2.2

(1) Age less than 20 years or more than 65 years.(2) Unable to sign a written informed consent or unwilling to cooperate.(3) They do not have the qualification for supporting Tibet or do not meet the basic requirements of medical examination for supporting Tibet.(4) There are acute or chronic illnesses, which will increase risk of injury from exposure to high altitude and hypoxia.

#### Withdrawal criteria

2.2.3

(1) Subjective willingness of withdrawal from the study because of various considerations after enrolment.(2) Patients cannot complete the experiment for any reason.

### Sample collection

2.3

#### Basic physiological parameters

2.3.1

With respect to physiological parameters, the blood pressure, heart rate, and fingertip arterial oxygen saturation of the medical personnel are monitored utilizing an electronic sphygmomanometer and a pulse oximeter, respectively. A body composition analyzer is employed to quantify body weight, body mass index (BMI), body age, visceral fat index, basal metabolic rate, and the percentage of fat and muscle in various body segments.

#### Cardiopulmonary function and fundoscopic examination

2.3.2

Regarding cardiopulmonary function assessment, a 12-lead electrocardiogram (ECG) device is utilized to examine the ECG conduction attributes, encompassing resting ECG and heart rate variability analysis. A cardiac function monitor is employed to assess cardiovascular function, including metrics such as heart rate, blood pressure, cardiac pumping and systolic functions, left heart workload, and peripheral vascular resistance. Pulmonary function testing is conducted to evaluate changes in maximum vital capacity, forced expiratory volume in one second (FEV1), and FEV1-to-forced vital capacity ratio (FEV1/FVC). Moreover, a 6-min walk test is administered to assess exercise endurance and cardiopulmonary function (13). Additionally, a fundoscopic examination is performed to inspect the vascular morphology of the fundus, to determine the presence of edema, and to ascertain any signs of hemorrhage (14).

#### Subjective assessments

2.3.3

Subjective assessments are conducted using the Lake Louise Acute Mountain Sickness Symptom Rating Scale to gauge the incidence of acute mountain sickness among the medical support staff in Tibet (15). The Adult Self-rating Health Scale is employed to evaluate scores for anxiety, depression, hostility, and somatization symptoms (16). The Pittsburgh Sleep Quality Index is utilized to assess alterations in subjective sleep quality (17). The Depression-Anxiety-Stress Scale is used to gauge the emotional state of the Tibetan medical professionals (18). Additionally, a questionnaire survey is conducted to evaluate the perception of oxygenation, oxygen comfort, thermal sensation, and thermal comfort under various experimental conditions (19).

#### Biological sample collection

2.3.4

For the procurement of blood, stool, urine, and oral samples, cubital vein blood is drawn for the analysis of hemoglobin concentration (20), hematocrit (HCT), and the calculation of the ratio of blood oxygen saturation to HCT. Further biochemical analyses included glucose (GLU), lipase (LIP), serum testosterone (T), ferritin (FERR), progesterone, vascular endothelial growth factor (VEGF), myoglobin (MYO), human interleukin-1β (IL-1β), total bilirubin (BILT), and alpha-amylase pancreatic (AMY-P) levels (21), as well as omics analyses. Fecal and oral samples are collected for subsequent metagenomic and fecal metabolomics high-throughput sequencing. Urine samples are analyzed for urinary α1-microglobulin (α1-MG), urinary β2-microglobulin (β2-MG), and microalbumin (mAlb) (22). Oral microbial community samples are obtained from participants prior to any eating, drinking, or tooth brushing upon waking in the morning. Sterile cotton swabs are used to thoroughly swab and rotate on the buccal mucosa, tongue base, and saliva, with the swab tips then placed in cryopreservation tubes and stored at −80°C pending metagenomic sequencing (23).

### Omics data analysis

2.4

#### Whole genome expression profiling of blood leukocytes

2.4.1

The acquired genomic data is subject to rigorous preliminary quality control measures, which entailed the elimination of low-quality reads and the excision of adapter sequences. Subsequent to these preprocessing steps, high-quality reads are aligned to a reference genome using established bioinformatics protocols, which may include tools such as STAR or Bowtie2. Gene expression levels are quantified through the application of bioinformatics tools such as HTSeq or Cufflinks. Differential expression analysis is conducted utilizing specialized statistical software, such as DESeq2 or EdgeR, to pinpoint genes exhibiting significant alterations in expression across various time points and environmental conditions, which may be implicated in the acclimatization to hypoxic stress.

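### Expression is profiled in mixed blood leukocytes with no differential count or composition adjustment listed, so a change in cell mix can be read as gene regulation

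*Protocol article*

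**What the plan says.** Section 2.1 (Design) of the protocol article includes "blood leukocyte whole gene expression profiling" among the planned analyses. No cell sorting or single-cell step is named anywhere in the article.

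Section 2.4.1 gives the processing chain: read quality control, alignment, quantification, then testing. On the test it says: "Differential expression analysis is conducted utilizing specialized statistical software, such as DESeq2 or EdgeR". No covariate is named. The purpose is to find "genes exhibiting significant alterations in expression across various time points and environmental conditions, which may be implicated in the acclimatization to hypoxic stress".

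Section 2.3.4 itemizes the blood measures. The only blood-cell measures are hemoglobin and hematocrit: "cubital vein blood is drawn for the analysis of hemoglobin concentration", with hematocrit next in the list. The rest are biochemical and hormonal: "Further biochemical analyses included glucose (GLU), lipase (LIP), serum testosterone (T), ferritin (FERR), progesterone, vascular endothelial growth factor (VEGF" and others. No white-cell count or differential appears.

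The results are then put to mechanistic use. Section 2.1 seeks the molecular pathways behind acclimatization. Section 2.4.6 feeds the omics layers into a network analysis that looks for hubs. The Discussion speaks of regulatory pathways and possible targets for prevention and treatment.

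**The concern.** A profile of mixed leukocytes is a weighted average over neutrophils, lymphocytes, monocytes and other cells. If the weights change between Beijing and Tibet, genes that mark one cell type change in the average even though no cell has altered its expression. Correct normalization and false-discovery control do not remove this, because the change in the average is real. What can go wrong is its interpretation.

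Genes marking the same cell type also move together. In section 2.4.6 such a set can look like a co-regulated module with hubs, and so become a candidate pathway or target. With neither a differential nor an estimate of proportions, a reader of the results could not tell which explanation applies.

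**Working it through.** The article gives no effect size, error rate or power for the expression analysis, so there is no figure of its own to reproduce. The calculation asks how often a gene would be flagged if composition changed and nothing was regulated.

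**Inputs.**
- From the article: 17 participants (section 2.2), each measured before departure and again at altitude, so 17 pairs if all complete.
- Assumed: the leukocyte shares, equal RNA yield per cell, an SD of the paired log2 difference of 0.3 to 0.5, and a per-gene threshold of p<0.001 as a rough stand-in for multiplicity control.

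**Step 1: a gene expressed in one cell type only.** Fold change = share after / share before.
- Lymphocytes 35% to 26%: 0.26/0.35 = 0.743; log2 = −0.429.
- Lymphocytes 35% to 30%: 0.30/0.35 = 0.857; log2 = −0.222.
- Neutrophils 55% to 65%: 0.65/0.55 = 1.182; log2 = 0.241.

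**Step 2: probability of p<0.001.** For a paired t-test with n = 17, the noncentrality is |log2 fold change| × √17 / SD, on 16 degrees of freedom, with a two-sided critical value of 4.015. For the first case at SD 0.3, this is 0.429 × 4.123 / 0.3 = 5.89, which gives 0.94.

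| Assumed shift | SD 0.3 | SD 0.4 | SD 0.5 |
|---|---|---|---|
| Lymphocytes 35% to 26% | 0.94 | 0.65 | 0.37 |
| Lymphocytes 35% to 30% | 0.23 | 0.09 | 0.04 |
| Neutrophils 55% to 65% | 0.30 | 0.11 | 0.05 |

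The meaning of the SD matters. If 0.3 is the SD of each single measurement, and errors are independent, the difference has SD 0.3 × √2 = 0.42. The SD 0.3 column then becomes 0.57, 0.07 and 0.09.

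**Step 3: a gene shared across cell types.** Let a cell class make up fraction f of the leukocytes, going from f0 to f1, and express the gene r times as strongly as the other cells. Then fold change = (f1·r + 1 − f1)/(f0·r + 1 − f0). With f0 = 0.55, f1 = 0.65 and r = 10, this is 6.85/5.95 = 1.15, flagged at p<0.001 with probability 0.17 at SD 0.3 and 0.03 at SD 0.5. With r = 2 it is 1.65/1.55 = 1.06, flagged with probability 0.012 and 0.004.

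**Step 4: many genes with false-discovery control.** A simulation used 2,000 genes, 40 repeats, Benjamini-Hochberg at 5%, baseline fraction 0.55 (between-person SD 0.07), SD of the within-person change in fraction 0.06, log2 r from N(0, 1.5), and residual SD of the paired log2 change 0.4. No gene was regulated.

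| Shift in fraction | Genes flagged, unadjusted | Genes flagged, adjusted for each person's change in fraction |
|---|---|---|
| 0 points | 0% | 0% |
| 5 points | 0% | 0% |
| 10 points | 2.7% | 0% |
| 15 points | 20.6% | 0% |

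The adjustment used the true fractions, which a real study would only estimate. The simulation held no truly regulated gene, so it does not show what adjustment costs in power.

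**The case against.** The strongest objection is that this is a condensed article. Section 2.4.1 fixes no model formula, and covariates or a deconvolution step could sit in a fuller plan. A differential may come with the same blood count as hemoglobin and hematocrit, and deconvolution can be run later on the expression data. That is fair, and it limits the point. It does not remove it: the article describes the expression chain down to adapter removal and itemizes the assays down to pancreatic amylase, yet composition decides what an altered gene means. A differential not kept at a visit cannot be taken afterwards.

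A reader might infer that composition shifts will be reported as genes regulated by hypoxia. The documents do not support that. They give no leukocyte data. The Introduction mentions adrenergic activation under acute hypoxia, which is a reason not to assume a stable mix but says nothing about the size of any shift. Section 2.4.1 claims only that altered genes may be involved. A changed cell mix may itself be part of acclimatization, so calling such genes altitude-related would be no error. The error would be to read them as transcriptional regulation.

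A reader might also infer that marker genes would dominate the list of hits. Under the assumptions above that is not so at 5 points, where the simulation flags almost nothing; the share becomes large only near 15 points.

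Last, composition may lie on the path from altitude to expression and overlaps with visit. Requiring genes to survive adjustment could discard true signals in 17 people. This objection stands, and the fix respects it.

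**Conclusion.** The point holds as a gap in what the results can show. With mixed leukocytes, no listed differential and no listed composition adjustment, the analysis in section 2.4.1 cannot separate a change in cell proportions from regulation inside cells, and section 2.4.6 carries that ambiguity into the network analysis.

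Its size is unknown from the documents. For single-cell-type marker genes it ranges from slight (0.04 for a small lymphocyte shift at SD 0.5) to near certain (0.94 for a moderate one at SD 0.3). These figures rest on assumed shares, assumed SDs, equal RNA per cell and 17 complete pairs. The plan should be changed because the remedy is cheap and the ambiguity bears on the study's mechanistic aim, not because a false result has been shown to be inevitable.

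**What to change.** 1. In section 2.3.4, state that the leukocyte differential from the blood draw is retained at each of the seven time points. If that is not possible, state in section 2.4.1 that proportions are estimated by deconvolution of the expression data. Deconvolution reuses the outcome data, so a measured differential is preferable.
2. Report the change in leukocyte composition over time as a result in its own right.
3. Show the DESeq2 or EdgeR results both without and with one or two composition terms, such as the neutrophil and lymphocyte shares. Describe genes that lose their signal after adjustment as possibly reflecting cell mix, and keep them in the report.
4. Carry that labelling into section 2.4.6, so that a module made up mainly of cell-type markers can be recognized.

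The cost is a few sentences of analysis wording, plus either keeping a count or one deconvolution run on existing data. The adjusted analysis gives up one or two degrees of freedom and some precision, because composition overlaps with visit. Showing both analyses side by side makes that loss visible.
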